### Procedures

Invitation letters will be sent to eligible patients 2 weeks prior to their outpatient appointment in the nurse-led botulinum toxin clinic by the trial co-ordinator. On the day of the appointment the patient will be approached by the research fellow to participate in the study. Those who agree will be consented into the trial by the research fellow. Qualitative data will be collected on reasons for refusal. Baseline assessment questionnaires will be given to participants consenting to take part in the study with a freepost envelope for return, all subsequent follow-up self-report questionnaires will be sent to the participants’ home also with a freepost envelope for return. Participants who do not return questionnaires within 2 weeks will be contacted by telephone. If participants do not respond to one follow-up telephone call and one letter, and there is no evidence that the patient has moved, it will be considered that they no longer wish to take part in the trial and they will not be sent further questionnaires. They will continue in the trial on the basis that clinical and cost-effectiveness data can still be collected and an intention-to-treat analysis (ITT) will be performed. Participants in the intervention trial arm who no longer wish to take part in the trial but are happy to continue to complete questionnaires will also be included in the ITT analysis.

Disease severity and function will be assessed at baseline and then at each clinic visit by the treating healthcare professionals and again 2 weeks after treatment via telephone by the research fellow.

Participants in the intervention group who have agreed to be contacted about an interview to assess acceptability of the new service will be followed up with a telephone call by a research assistant to arrange a time and place for the interview. Participants will be interviewed after their 9-month participation in the trial has ended.

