### Intervention

Participants randomised to the intervention group will initiate their own treatment during the trial period (9 months). They will be given information about when and how to initiate an appointment in the nurse-led botulinum toxin clinic, in a leaflet sent to them by a trial co-ordinator after randomisation. Participants will be asked to contact the service when they feel their symptoms are returning at a sufficient level for them to seek medical help. Contact details for the service will also be provided along with information on how quickly an appointment will be made, with whom, and the procedure in the case of an emergency. Receipt of the leaflet will be followed by a telephone call from one of the research team to answer any questions participants may have. When participants in the intervention group contact the service to book an appointment they will be triaged by the trial co-ordinator. All patients with an activity score of 1 or above on the Jankovic Rating Scale (JRS; [12]) will be booked in to the next available slot within the twice-weekly nurse-led outpatient clinics, estimated within a 2-week period from the initial call. There will be no upper limit for the number of times participants in the intervention group can initiate an appointment. However, participants will be advised to wait 2 weeks after botulinum toxin treatment as this is the time it takes to reach effectiveness. It is, therefore, estimated that participants would not return to the clinic within 3 to 4 weeks of their previous appointment. All participants will be given an appointment at 9 months to meet safety criteria for any patients who do not seek an appointment during their participation in the trial.

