##### Functional disability

The Blepharospasm Disability Index (BSDI)© [15, 16] is a patient self-report measure that asks about six daily activities: reading, driving a vehicle, watching TV, shopping, walking and doing everyday activities. The measure is also recommended for use in hemifacial spasm [14]. Each activity is rated on a scale from 0 = no impairment to 4 = no longer possible due to my illness, and a ‘not applicable’ option is also available. The scoring system is a mean item score, calculated by dividing the sum score by the number of applicable items. Sum scores, therefore, range from 0 to 4 with higher scores indicating greater disability. A 0.7-point improvement in the BSDI© mean item score is considered a clinically relevant improvement [13]. However, this criteria is only relevant for patients whose baseline scores are >0.7 [13]. The measure possesses good convergent validity with the JRS, good internal consistency (Cronbach’s alpha = 0.88) and adequate test-retest reliability [13].

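### Silence after the 3-month pack, one call and one letter is treated as withdrawal from questionnaires, which needlessly loses the 9-month satisfaction score, a primary outcome

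*Protocol article*

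**What the plan says.** The rule stands in Procedures and works in steps. First, "Participants who do not return questionnaires within 2 weeks will be contacted by telephone". Then, "If participants do not respond to one follow-up telephone call and one letter, and there is no evidence that the patient has moved", the consequence is that "it will be considered that they no longer wish to take part in the trial and they will not be sent further questionnaires".

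The next sentence keeps these people in the study: "They will continue in the trial on the basis that clinical and cost-effectiveness data can still be collected", under an intention-to-treat analysis. Intervention participants who actively leave but are willing to go on completing questionnaires are also kept in that analysis.

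Other parts of the article bear on what is lost:

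- Outcomes places self-report follow-up at 3 and 9 months only, and Procedures sends follow-up questionnaires by post.
- Patient satisfaction makes the CSQ a primary outcome. No clinic or telephone route is given for it.
- Functional disability describes the BSDI, another primary outcome, which "is a patient self-report measure that asks about six daily activities".
- Procedures also states: "Disease severity and function will be assessed at baseline and then at each clinic visit by the treating healthcare professionals". The research fellow repeats the assessment by telephone two weeks after each treatment.
- Data monitoring has the external monitor check collection of both the Jankovic Rating Scale (JRS) and the BSDI at each time point.
- Intervention states: "All participants will be given an appointment at 9 months to meet safety criteria". Patient safety adds that participants are booked back automatically at the end of the trial period.

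**The concern.** Failing to answer is not a decision to withdraw, yet the rule treats it as one for questionnaires while treating the same person as a continuing participant for everything else. With only two follow-up rounds, the one mailing that the rule saves after a silent 3-month round is the final one. A gap that might have been intermittent becomes permanent at the last time point.

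The main exposure is the CSQ. Participants know their allocation (Blinding) and are rating the care model they were given. Their willingness to reply may therefore depend on how satisfied they are, and may do so differently in the two arms. An analysis plan cannot recover data that were never requested.

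**Working it through.** **1. Who is caught.** Four conditions must all hold: no return within 2 weeks, no response to the call, no response to the letter, and no sign of a change of address. Late returners, people reached by telephone or letter, and people known to have moved are not caught.

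**2. Which outcomes are exposed.**

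| Outcome | Stated route | 9-month value under the rule |
|---|---|---|
| JRS (primary) | Clinician-rated at clinic visits | Not affected |
| BSDI (primary) | Self-report; function also assessed at clinic visits and by telephone; collection monitored | Probably kept, but not stated outright |
| CSQ (primary) | Questionnaire only | Lost |
| CDQ-24, HADS and other questionnaire-only secondaries | Questionnaire only | Lost |

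**3. What the model retains.** Changes over time fits arm, time (0, 1, 2) and their interaction by REML. A participant silent from 3 months contributes a baseline CSQ and nothing after randomisation. Incomplete records are handled validly if data are missing at random, but here that assumption conditions on the baseline score alone. If the plan's ICC of 0.3 (Sample size) is taken as the baseline-to-9-month correlation of the CSQ, which is an assumption, baseline explains about 0.3² = 9% of the variance of the missing score.

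**4. How many records.** The article has no figure for this to reproduce. The nearest is the 79% completion rate in Sample size, a 21% loss, which is overall non-completion and not silence at 3 months. The inputs are therefore assumed:

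- N = 266 (Abstract)
- p = share caught by the rule after the 3-month pack, 10% to 21%
- q = share of those who would return a 9-month pack if sent one, 20% to 50%

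Avoidable loss = N × p × q:

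- Low: 266 × 0.10 × 0.20 = 5.3, about 5 (2.0%)
- Middle: 266 × 0.15 × 0.35 = 14.0, about 14 (5.2%)
- High: 266 × 0.21 × 0.50 = 27.9, about 28 (10.5%)

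**5. How much bias is possible.** Let f1 and f0 be the shares of each arm lost at 9 months, and let those lost differ from those observed by D1 and D0 standard deviations. The complete-case bias in the arm difference is f1 × D1 − f0 × D0. With a common D this is (f1 − f0) × D:

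- Equal loss in both arms: 0
- 20% against 10% lost, D = 0.25: 0.10 × 0.25 = 0.025 SD
- 20% against 10% lost, D = 0.50: 0.10 × 0.50 = 0.05 SD

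Mailing the 9-month pack would remove part of any such bias, not all of it, because only the share q comes back.

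**The case against.** The strongest defence is that the rule is open, identical in both arms and limited. It applies only after a call and a letter, it spares people who repeatedly do not reply from further approaches, and clinical follow-up and the intention-to-treat analysis continue. Limiting respondent burden is a legitimate choice. That stands as a reason for having some contact limit. It does not explain why silence at 3 months should cancel a single mailing six months later.

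Four stronger readings are tempting, and the article does not support them.

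- *Missing one questionnaire round removes a participant.* It does not. The call, the letter and the check for a move come first.
- *The 9-month BSDI is discarded.* Function is assessed at each clinic visit and by telephone, BSDI collection is monitored, and everyone has a 9-month appointment. The likelier reading is that it continues. What remains open is that Procedures never says the clinic assessment of function is the BSDI, or which reading supplies the 9-month value.
- *The intention-to-treat comparison is biased.* Bias needs non-response that relates to satisfaction and differs by arm. Neither is shown, and under equal loss with a common D the bias is zero.
- *The lost records add to a shortfall in completers.* At 79% completion, 266 gives about 210, some 20 fewer than the 230 of Scenario 1. That gap already allows for 21% non-completion, which can include these same people. Setting 5 to 28 records against it would count them twice.

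It is also fair to say that q is uncertain. It concerns people who ignored a pack, a call and a letter, and nothing in the article indicates how many of them would reply later.

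A further caution concerns the remedy. The CSQ rates the clinic itself and the treating staff are not masked, so completing it there could draw more favourable answers than completing it at home.

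**Conclusion.** The point holds in a limited form. The rule causes avoidable loss of 9-month CSQ scores, a primary outcome, and of questionnaire-only secondaries, from participants who remain in the trial. The loss is about 5 to 28 of 266 records (2% to 10.5%), resting wholly on the assumed p of 10–21% and q of 20–50%. Possible bias runs from zero to about 0.05 SD if loss differs by 10 percentage points between arms and those lost differ by up to 0.5 SD. The multilevel model gives only weak protection, since these participants have no CSQ score after randomisation. The JRS is unaffected, and for the BSDI a clarification is needed. This is a worthwhile, inexpensive improvement and not a flaw that undermines the trial.

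**What to change.** Amend Procedures as follows:

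1. State that non-response to a questionnaire round is not withdrawal. Stop questionnaires only for participants who actively decline them.
2. Mail the 9-month pack to every other participant, in both arms alike, with the CSQ placed first.
3. As a fallback only, for those who still do not reply, offer sealed self-completion at the existing 9-month visit. Treating staff should not handle it, and the mode of completion should be recorded so that its influence can be examined.
4. Say whether the clinic assessment of function is the BSDI, and which reading is the 9-month value.

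The cost is a minor wording amendment, postage, and a few minutes at a visit that already takes place. Some non-responders receive one more mailing. Any scores completed in clinic may differ by mode, which is why the postal pack should remain the main route.

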### Data monitoring

Data collection will be monitored by an external monitoring agency experienced in NHS Research and Development (R&D) processes. The following will be monitored: collection of the JRS and BSDI© at each time point, identification of adverse events not recorded and the appropriate recording of telephone calls from patients requesting appointments. The first monitoring visit will take place shortly after recruitment commencing to identify issues early into the study and resolving these promptly. A single further follow-up visit will be scheduled to take place 6 months after the first.

### Patient safety

Patient safety will be monitored by the specialist research nurse treating patients and the research fellow. Participants will be automatically booked back into the nurse-led botulinum toxin clinic at the end of the trial period by the trial co-ordinator. Reasons for not initiating treatment during participation in the trial will be recorded for any patients who have not attended for the full duration and all patients will continue to receive standard care.

### Sample size

Sample size for multilevel modelling (MLM) was estimated by simulating a range of scenarios using the software Power and Precision™ (Version 4.1; [32]). Using a large ICC of 0.3 [33], time as nested within participants, and setting power at 80 %, it was estimated that between 92 and 230 participants would be required with small to medium effects (Table 2). Based on a 79 % completion rate [9] this would mean that between 112 (56 per group) and 278 (139 per group) will need to be consented into the trial.

**Table 2 Tab2:** Sample size estimation based on four scenarios with small to medium effect sizes

Scenario	Effect size (*d*)	ICC	Standard care	Intervention	Time points	Alpha	Tails	Power
Scenario 1	0.25	0.3	115	115	4	0.05	2	0.80
Scenario 2	0.3	0.3	80	80	4	0.05	2	0.80
Scenario 3	0.35	0.3	59	59	4	0.05	2	0.80
Scenario 4	0.4	0.3	46	46	4	0.05	2	0.81

The qualitative study assessing acceptability of the new service aims to recruit an initial sample of 10 participants with a stopping criterion of a further three interviews to confirm that data saturation has been achieved [34]. Data saturation is defined as the emergence of no new themes in relation to the research question.

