### Outcomes

Participants will be in the trial for 9 months. An initial baseline assessment will be taken by a research fellow prior to randomisation; this will include the full range of measures. Self-report measures will be taken again at 3- and 9-month follow-ups.

At baseline, demographic information will be collected using self-report measures including: date of birth, gender, marital status, ethnicity, postcode, number of years of schooling, highest completed level of education and further education. Data will also be collected from the patients’ medical notes on diagnosis, year of diagnosis, duration of botulinum toxin treatment, number of previous cycles, frequency of previous cycles, last dose, and co-morbidities. The total number of botulinum toxin injections and dosage received by the patient across the trial period will be collected.

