#### Changes over time

In order to explore stability in the primary outcome measures over the treatment period, and change in satisfaction, quality of life, mood and illness and treatment beliefs, multilevel models (MLM) will be employed. Time will be nested within participants and to check the assumption that scores within a participant are highly correlated, the first MLM will include no predictors and a scaled identity covariance type for both level 1 and level 2 in order to calculate the intraclass correlation coefficient (ICC). Models will be fitted with a first order autoregressive (AR1) covariance structure. Restricted Estimate Maximum Likelihood (REML) methods will be used as these are preferred for smaller samples [35].

Trial arm (0 = control, 1 = intervention), time (0, 1, 2) and the interaction between trial arm and time will be entered as fixed effects in each model, with participant identification number as a random effect. A significant interaction term will be interpreted as evidence for differential treatment effectiveness. Pairwise comparisons will be performed in order to establish where the significant differences lie, using estimated marginal means and standard errors. Standardised adjusted effect sizes for group differences at each time point will be calculated using Hedges’ *g* along with 99 % confidence intervals (as *p* < 0.01) using the formula provided by Turner and Bernard [36]. Hedges’ *g* includes a correction factor for small samples which, if absent, may lead to a less accurate and upwardly biased effect size. These effect sizes are interpreted in the same way as Cohen’s *d* [37] (small = 0.20, medium = 0.50, large = 0.80).

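### Table 2 is sized on four time points and matches a time-averaged arm effect, but the planned analysis uses three time points and an arm-by-time interaction, so the stated 80 % power does not belong to the deciding test

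*Protocol article*

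**What the plan says.** In the Protocol article, Sample size, Table 2 gives four scenarios, all with ICC 0.3, two-sided alpha 0.05 and four time points. The columns are scenario, d, ICC, n in standard care, n in intervention, time points, alpha, tails and power. The first row reads "Scenario 1 0.25 0.3 115 115 4 0.05 2 0.80" and the last "Scenario 4 0.4 0.3 46 46 4 0.05 2 0.81". From these rows "it was estimated that between 92 and 230 participants would be required with small to medium effects". The section says that scenarios were simulated in named software with time nested within participants. It does not say whether d is a main effect, a change or an interaction.

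Under Outcomes, after the baseline assessment, "Self-report measures will be taken again at 3- and 9-month follow-ups". Under Statistical methods, Changes over time, "time (0, 1, 2) and the interaction between trial arm and time will be entered as fixed effects in each model". The decision rule follows: "A significant interaction term will be interpreted as evidence for differential treatment effectiveness". The same section specifies an AR(1) covariance structure.

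The Abstract gives a recruitment target of 266, and the Sample size section assumes 79 % completion.

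**The concern.** The sample-size basis and the planned analysis differ in two ways. Table 2 counts four measurements per participant where the model has three, of which only two follow randomisation. Also, the sizes look like those for an arm difference averaged over time, whereas the deciding test asks whether the arm difference changes over time. With no arm difference at baseline, that test is in effect a comparison of changes from baseline. At a modest within-person correlation this contrast has a much larger variance than an averaged mean.

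If the stated power does not apply to the deciding test, a non-significant interaction could be read as evidence against patient-initiated care when the trial had well under 80 % power for the smaller effects it was planned around.

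**Working it through.** **Inputs.** From Table 2: d = 0.25, 0.30, 0.35, 0.40 with n = 115, 80, 59, 46 per arm; ICC 0.3; alpha 0.05 two-sided; four time points. From Changes over time: three time points, interaction test, AR(1). From the Abstract and Sample size: 266 recruited, 79 % completion.

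**Formulas.** In single-occasion SD units, 1-df power = Φ(d/√(2F/n) − 1.96), where F is the variance factor of the contrast. The 2-df test uses a noncentral chi-square with noncentrality λ.

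**1. Reproducing Table 2.** For an arm difference averaged over four exchangeable measurements, F = (1 + 3×0.3)/4 = 0.475. At d = 0.25 and n = 115: √(2×0.475/115) = 0.0909, 0.25/0.0909 = 2.75, power 78.5 %. The four rows give 78.5, 78.6, 78.8 and 79.5 %. Solving 2(1.96 + 0.8416)²×0.475/d² gives 120, 83, 61 and 47 per arm, slightly above the table.

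A baseline-adjusted mean of three follow-ups also fits. F = (1 + 2×0.3)/3 − 0.3² = 0.443, which gives 112, 78, 57 and 44 per arm, with power 81.3-82.2 % at the stated n.

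Interaction readings with four time points do not fit: 35 % (3 df) and 50-51 % (1 df).

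**2. Three time points instead of four, same kind of effect.** F = (1 + 2×0.3)/3 = 0.533, power 74-75 %.

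**3. The planned interaction.** Assume no arm difference at baseline, d at both follow-ups, and exchangeable correlation r = 0.3.
- Mean of two follow-ups minus baseline: F = (1 + r)/2 + 1 − 2r = 1.05.
- 2-df test: λ = d²n/(2×1.05). At d = 0.25 and n = 115, λ = 3.42.

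| d | n per arm | Table 2 power | Averaged arm effect, 4 points | Interaction, 2 df | Average change, 1 df |
|---|---|---|---|---|---|
| 0.25 | 115 | 80 % | 78.5 % | 36 % | 46 % |
| 0.30 | 80 | 80 % | 78.6 % | 36 % | 46 % |
| 0.35 | 59 | 80 % | 78.8 % | 36 % | 46 % |
| 0.40 | 46 | 81 % | 79.5 % | 37 % | 47 % |

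The 2-df test needs λ = 9.63 for 80 % power. At d = 0.25 that is 9.63×2.1/0.25² ≈ 324 per arm.

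**4. Sensitivity, same pairs of d and n.**
- AR(1) with correlation 0.3: F = 0.65 + 1 − (0.3 + 0.09) = 1.26. Power is 31-32 % (2 df) and 39-40 % (1 df).
- Exchangeable 0.7: F = 0.85 + 1 − 1.4 = 0.45. Power is 72-73 % (2 df) and 81-82 % (1 df).
- Effect building linearly to d at 9 months, exchangeable 0.3: about 28 % (2 df).

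**5. At the recruitment target.** 266×0.79/2 ≈ 105 per arm. With r = 0.3, d = 0.25 gives λ = 0.0625×105/2.1 = 3.13 and 33 % power; d = 0.40 gives λ = 0.16×105/2.1 = 8.0 and 72 %. The 1-df figures are 42 % and 81 %.

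**6. Detectable d at 80 % power, r = 0.3.**
- 2-df interaction: √(9.63×2.1/n) = 0.42 at 115 and 0.44 at 105 completers per arm.
- Baseline-adjusted mean of 3 and 9 months: F = 0.65 − 0.09 = 0.56, so d = 2.80×√(2×0.56/n) = 0.28 and 0.29.

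**The case against.** Four arguments can be made for the plan.

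- **The method behind Table 2 is not stated.** A reader might infer that it was certainly computed as an arm main effect over exchangeable measurements. The article does not say so. The simple formula is slightly above the table in every row, and a baseline-adjusted calculation fits as well. This stands, but both readings that fit are time-averaged arm effects and no interaction reading tried comes near.
- **The low power figures are conditional.** They need a constant effect in single-occasion SD units and a correlation of 0.3. The plan itself expects scores within a participant to be highly correlated, and a higher correlation raises interaction power. This stands too. However, 0.3 is the document's own planning value, and the specified AR(1) structure at that value gives less power, not more.
- **Four occasions may exist for some outcomes.** Procedures has severity and function assessed at every clinic visit and again two weeks after treatment, and usual-care visits are about three-monthly. So the documents do not support saying that a four-occasion design is impossible. But intervention visits are timed by the patient, satisfaction is a questionnaire measured at three points, and the analysis codes three levels in each model. Even with four points the interaction would reach only 35-51 %.
- **No single target effect is named.** A reader might infer that the trial has little chance of detecting what it was designed for. That goes too far: at 105 per arm and d = 0.40 the interaction has 72 % (2 df) or 81 % (1 df).

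**Conclusion.** The concern holds as a mismatch between the sample-size basis and the deciding test. The disagreement on time points is in the text. The disagreement on the tested effect is inferred from what reproduces Table 2, and the inference is firm because every reading that fits is a time-averaged arm effect.

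At the document's own d, n, alpha and ICC, the planned interaction does not deliver the stated 80 %. The shortfall is roughly half, on the assumptions of a constant follow-up effect, no baseline difference and exchangeable correlation 0.3. No single percentage should be read as the trial's power, because the result moves with the correlation, its structure and the shape of the effect. Most of the loss comes from the tested effect: going from four points to three costs only about 4 to 5 percentage points.

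**What to change.** Reconcile Sample size with Changes over time. State which effect d measures, how many time points enter the model, and which contrast decides effectiveness. Then recompute Table 2 for that contrast, keep the recruitment target, and report power or detectable effect at about 105 completers per arm over a range of within-person correlations and for the AR(1) structure.

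If the 2-df interaction stays, the detectable d to report at ICC 0.3 is the 0.42 to 0.44 shown above. The cost is a rewritten paragraph and table, with a less favourable figure and no extra patients.

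Optionally, the sponsor could make the baseline-adjusted arm difference averaged over 3 and 9 months the deciding contrast, with a detectable d of about 0.28 to 0.29. This costs more than rewording. It replaces the decision rule in the analysis section, and it tests a mean difference, whereas the first primary aim in the Background is a steadier course of severity and disability. The choice should be made and justified before unblinding.

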**Methods/Design:**

A randomised controlled trial will compare a patient-initiated model of care, where patients determine botulinum toxin treatment timing, to the standard model of care in which care is scheduled by the clinical team. A sample of 266 patients with blepharospasm or hemifacial spasm will be recruited from Moorfields Eye Hospital (MEH), London. The trial will be accompanied by a mixed-methods evaluation of acceptability of the new service. Patients who meet eligibility criteria will be assessed at baseline and those in the intervention group will be provided with instructions on how to book their own treatment appointments. Patients in both groups will be followed up 3 and 9 months into the trial and all patients will be returned to usual care after 9 months to meet safety protocols. Primary outcome measures include disease severity (questionnaire), functional disability (questionnaire) and patient satisfaction with care (questionnaire). Secondary outcomes include disease-specific quality of life (questionnaire), mood (questionnaire), illness and treatment perceptions (questionnaire and semi-structured interviews), economic impact (questionnaire) and acceptability (questionnaire and semi-structured interviews).

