### Randomisation

Randomisation (1:1) will be undertaken by a central randomisation service by the data management team at Moorfields Eye Hospital (MEH) in order to ensure the research fellow collecting and analysing the data is blinded to group allocation. Participants will be randomised to receive either treatment as usual or patient-initiated follow-up appointments. Randomly permutated blocks of varying sizes will be employed to ensure balance between treatment groups. Due to the nature of the nurse-led botulinum toxin clinic it will not be possible to blind the treating healthcare professionals from group allocation. The trial co-ordinator will staff the telephone line that participants in the intervention group will use to book their appointments and, as such, the trial co-ordinator will not be blinded to group allocation.

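### The allowance for 21 % non-completion multiplies by 1.21 instead of dividing by 0.79, so 112 to 278 should read 118 to 292, and the abstract's 266 is tied to no scenario

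*Protocol article*

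**What the plan says.** The Sample size section of the protocol article starts from four scenarios in Table 2. The most demanding row reads "Scenario 1 0.25 0.3 115 115 4 0.05 2 0.80" and the least demanding reads "Scenario 4 0.4 0.3 46 46 4 0.05 2 0.81". From these the text concludes that "it was estimated that between 92 and 230 participants would be required with small to medium effects".

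It then allows for attrition. "Based on a 79 % completion rate", it says, "this would mean that between 112 (56 per group) and 278 (139 per group) will need to be consented into the trial".

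The abstract (Methods/Design) gives a single figure: "A sample of 266 patients with blepharospasm or hemifacial spasm will be recruited". That number does not appear in the Sample size section, and neither place says which scenario sets the target. Allocation is equal: "Randomisation (1:1) will be undertaken by a central randomisation service".

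**The concern.** If a fraction 0.79 of consented patients complete, the number to consent is the required number of completers divided by 0.79. Multiplying by one plus the dropout rate is a common slip and always gives too few. The stated range looks like the result of that slip. If so, the section's claim that these numbers suffice at 79 % completion is untrue at both ends of the range.

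A second matter sits beside it. The abstract commits to 266, and a reader cannot tell from the article where that figure comes from or which effect size it is meant to detect. The recruitment total and its justification are what the finished trial will be judged against, so they should be correct and agree with each other.

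**Working it through.** **Inputs.** All are from the Sample size section and Table 2, except 266 (abstract) and 1:1 allocation (Randomisation).

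- Scenario 1: d = 0.25, 115 per arm (230 in total), power 0.80.
- Scenario 2: d = 0.3, 80 per arm.
- Scenario 3: d = 0.35, 59 per arm.
- Scenario 4: d = 0.4, 46 per arm (92 in total), power 0.81.
- All scenarios: ICC 0.3, 4 time points, two-sided alpha 0.05.
- Completion 79 %, so non-completion 21 %.

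**Step 1: the numbers before attrition.** With four equally correlated measurements, the variance factor is (1 + 3 × 0.3)/4 = 0.475. The two-group formula with this factor gives 120, 83, 61 and 47 per arm, against the stated 115, 80, 59 and 46. Power at the stated numbers is 78.5 % to 79.5 %, within two points of the stated 80 % or 81 %. The plan used simulation software, so I accept 92 to 230 as given.

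**Step 2: reproduce the stated consent figures.** Multiply each arm by 1 + 0.21:

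- 46 × 1.21 = 55.66, rounded to 56 per group, 112 in total.
- 115 × 1.21 = 139.15, rounded to 139 per group, 278 in total.

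Both ends match exactly.

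**Step 3: the correct inflation.** Divide each arm by 0.79 and round up:

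| Scenario | Required per arm | ÷ 0.79 | Consent per arm | Total |
|---|---|---|---|---|
| 1 | 115 | 145.6 | 146 | 292 |
| 2 | 80 | 101.3 | 102 | 204 |
| 3 | 59 | 74.7 | 75 | 150 |
| 4 | 46 | 58.2 | 59 | 118 |

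The stated 112 and 278 are 6 and 14 short. Rounding does not explain gaps of that size.

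**Step 4: completers expected at 79 %.**

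- 112 × 0.79 = 88.5, against 92 required.
- 278 × 0.79 = 219.6, against 230 required.
- 266 × 0.79 = 210.1, or 105 per arm.

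The figure 266 equals none of 112, 278, 118 or 292. It exceeds the 204 needed for Scenario 2, and so also covers Scenarios 3 and 4. It is 26 below the 292 needed for Scenario 1.

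**Step 5: power if Scenario 1 is the target.** I calibrate to the plan's own statement that 230 completers give 80 % power at d = 0.25. The expected test statistic is then 1.960 + 0.842 = 2.802 at 230 completers and scales with the square root of the number of completers.

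- 278 consented: 2.802 × √(219.6/230) = 2.738. Subtracting 1.960 leaves 0.778, so power is about 78 %.
- 266 consented: 2.802 × √(210.1/230) = 2.678. Subtracting 1.960 leaves 0.718, so power is about 76 %.
- Effect detectable at 80 % power: 0.25 × √(230/219.6) = 0.256 for 278, and 0.25 × √(230/210.1) = 0.262 for 266.

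**The case against.** The attrition arithmetic has no good defence. What can be contested is how much follows from it.

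**266 as a target that misses its mark.** A reader might infer that 266 was meant to deliver 230 completers and falls 20 short. The document does not say so. It gives a range over four scenarios and never names Scenario 1 as the design target. The figure 266 lies inside the stated 112 to 278, and even after correct inflation it covers three of the four scenarios. The shortfall against 230 is explicit only for 278. This objection stands, so any power loss for 266 is conditional on Scenario 1 being intended.

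**Two contradictory totals.** This too overstates the case: one place gives a range and the other a single value within it. The full protocol, which is not shown, may explain the choice. What remains is that the article commits to a number its own sample-size section neither derives nor links to a scenario.

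**A larger power loss.** The two-group formula of Step 1 gives about 75 % power and a detectable effect of about 0.27 at 105 per arm. But that formula gives only 78.5 % at 115 per arm, where the plan states 80 %. Setting its results against the plan's 80 % mixes two baselines and exaggerates the loss.

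**Non-completers are not wholly lost.** Under Procedures, patients who stop returning questionnaires stay in the trial for clinical and cost data and are analysed by intention to treat. The JRS, a primary outcome, is clinician-reported and taken at clinic visits. The multilevel model can use partial follow-up. This stands as well: the losses in Step 5 are upper bounds, more so for the JRS than for the questionnaire outcomes. It does not rescue the stated range, because the plan itself chose to inflate for non-completion.

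**Conclusion.** The consent range is wrong on the plan's own inputs. It should be 118 (59 per group) to 292 (146 per group), not 112 to 278. This rests only on the stated 79 % completion rate and the Table 2 numbers, taken as given.

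The 266 in the abstract lacks a derivation and a scenario. The document does not support calling it a failed target.

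The practical loss is modest. In the most demanding scenario it is at most about 2 points of power at 278 and about 4 points at 266, assuming that the plan's 80 % at 115 per arm is right and that non-completers contribute nothing. The stated figures should be corrected, but the error does not undermine the design or the analysis.

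**What to change.** - In the Sample size section, replace 112 (56 per group) and 278 (139 per group) with 118 (59 per group) and 292 (146 per group), and state that the required numbers were divided by 0.79.
- Give one reconciled recruitment total in the abstract and in the Sample size section, and name the Table 2 scenario it serves.
- If 266 is kept for Scenario 2, 3 or 4, say so. It exceeds what each of these needs.
- If 266 is kept and Scenario 1 is intended, state that it yields about 210 completers (105 per arm), with about 76 % power at d = 0.25 or 80 % power at about d = 0.26. Add that this treats non-completers as contributing no data.

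The cost is a correction of stated figures. Keeping 266 needs no extra patients and no change to design or analysis. Holding 80 % power at d = 0.25 with 79 % completion would instead take 292, which is 26 more than the abstract states.
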